## INTRODUCTION

Spinal muscular atrophy (SMA) is a neurogenetic disorder caused by loss of or pathogenic variants in the survival motor neuron 1 gene (*SMN1*) on chromosome 5q13, which leads to reduced SMN protein levels and a selective dysfunction of motor neurons. SMA is an autosomal recessive spectrum of disorders, with an estimated incidence of 1:10,000 live births, 60 percent of which is the most severe form, SMA Type 1. SMA is the leading cause of infant mortality among genetic diseases [1]. *SMN2* is a paralogous gene that is present in all patients and is considered a phenotype modifier. Multiple copies of *SMN2* are associated with milder phenotypes [2]. Over the last 10 years, there have been numerous publications describing the natural history of patients with SMA and the effects of available supportive therapies [3– 14].

Until recently, supportive medical care was the mainstay of treatment for patients with SMA. Results from recent clinical trials of gene therapy, antisense oligonucleotides, and small molecules have demonstrated that these interventions can alter the course of disease [15– 20]. At the same time, standard of care guidelines have been published that support proactive intervention [15, 21, 22].

There is a need for long-term efficacy and safety information from patients receiving both existing and new therapies to document the evolving trajectory of SMA and the impact of these treatments on patient and caregiver outcomes as well as on the healthcare system. These findings promise to enhance data from long-term extensions of completed and ongoing clinical trials [23, 24]. In addition, evolving therapies raise several questions with direct impact on daily practice, such as the best prognostic factors, early identification of likely responders, reasonable expectations regarding treatment outcomes, durability of therapeutic response, and approaches to combining established and emerging therapies. Results from clinical trial extensions can be supplemented and extended by longitudinal registry data, which can play an important role in redefining the natural history of a disease resulting from the availability of disease-modifying therapies [25].

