### Treatment

The choice of ongoing medical treatment for the duration of the Registry will be made independently by the physician in the course of regular patient care and will not be influenced by participation in this Registry. Physicians are free to add or withdraw any medication but will continue to monitor each patient for the full 15 years, until death, or until the patient is withdrawn from the Registry, which may occur at the discretion of the patient or the patient’s parent/legal representative or physician. No treatments will be provided by the sponsor as part of participation in this Registry.

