## DISCUSSION

RESTORE is a prospective, treatment-independent, collaborative global registry. It will recruit patients from a variety of settings and backgrounds allowing assessment of short- and long-term outcomes representative of the contemporary treatment of patients with a confirmed diagnosis of SMA. To permit evaluation of patients who receive gene therapy with onasemnogene abeparvovec, this Registry will recruit patients who were previously treated in a formal clinical study or EAP/MAP.

The primary objective of the Registry is to gather long-term follow-up information on patients’ outcomes that cannot be collected in the time frame of a typical clinical trial. Contemporary follow-ups from EAP programs [31, 33, 34] or clinical trials [15, 17, 18] do not exceed 2 years and include only patients treated with a single approach. The potential importance of inclusion of patients receiving multiple therapies is underscored by an example from the treatment of Duchenne Muscular Dystrophy, in which a registry enrolling a patient who received several therapies could permit comparison of the long-term efficacies of deflazacort and prednisone [35], and better assess the efficacy of daily treatment when compared to alternative regimens [36].

In addition, long-term data collection from a large patient sample may provide important insights regarding prognostic factors, characteristics of best responders to therapies, and estimation of the duration of unsuccessful treatment after which a patient can be considered a non-responder. Another very important question that can only be assessed by long-term follow-up is the need for and the cost-effectiveness of treating pre-symptomatic patients. Even if there are few or no questions about this approach in patients with 2 or 3 *SMN2* copies [37], this question will undoubtedly arise for patients with 4 copies, reflecting the creation of numerous newborn screening programs [38– 40]. The issue of treating presymptomatic patients has also been raised in late-onset Pompe disease [41] and this question should be addressed generally. Another important consideration related to treatment of asymptomatic patients, who are potential candidates for gene therapy, is the persistence of transgene expression, which can be determined over long-term follow-up of Registry patients.

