Because patients will not be randomized, statistics will be limited to comparisons of means, frequencies, and temporal trends. The prognostic factors for key milestones, including sitting for the SMA type 1 patients, or walking for type 2 and type 3 patients, will be investigated by comparing proportions of sitters and walkers according to multiple parameters, including disease duration, number of *SMN2* copies, baseline conditions, etc. Our focus will be on assuring the representativeness of patients, completeness of the information collected for each patient, and the validity of study data.

Due to uncontrolled variations in scheduling follow-up care, data cannot be collected at fixed intervals. Even if all families are offered similar standards of care, some may refuse all or a portion of this support, and variations in Registry findings will reflect the heterogeneity of care delivered. In addition, some patients may choose to enroll in controlled clinical trials during the follow-up period. Loss to follow up, independent of patient status, represents another challenge for data collection and assessment.

Strengths of our design include a focus on enrolling consecutive eligible patients who were genetically diagnosed, representing a broad range of evolving SMA care practices and outcomes across many countries and health care systems. This should provide a robust characterization of the course of disease for patients with SMA receiving the full range of contemporary and evolving treatments and supportive care. Additional strengths of an observational study design include the option to modify the registry design as standards of care are advanced and experience is gained from the care of patients receiving interventions that greatly extend the lifespans of SMA patients. During the planned 15-year duration of the Registry, additional variables may be added to the data collection forms, leading to important insights into questions that were not anticipated in the original study design.

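### Prognostic factors for sitting and walking are to be examined by comparing proportions only, with no stated account of therapy, so the results will depend on prescribing patterns

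*Protocol article*

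**What the plan says.** The Discussion of the protocol article sets a general limit: "Because patients will not be randomized, statistics will be limited to comparisons of means, frequencies, and temporal trends". The next sentence applies it to prognostic factors for key milestones, sitting in type 1 and walking in types 2 and 3. These "will be investigated by comparing proportions of sitters and walkers according to multiple parameters". The parameters given are disease duration, number of SMN2 "copies, baseline conditions, etc", so the list is left open. Therapy is not named in it.

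The Data analysis section stratifies by therapy at enrollment, but states this for the primary summary of outcomes. It announces no formal hypothesis testing.

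The Treatment section says that the choice of therapy "will be made independently by the physician in the course of regular patient care", and lets physicians add or withdraw medication during follow-up. The Introduction says that recent therapies can change the disease course and that multiple SMN2 copies "are associated with milder phenotypes". Among the practical questions raised by evolving therapies it lists some "such as the best prognostic factors, early identification of likely responders".

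**The concern.** The article gives lack of randomisation as the reason to keep to simple comparisons. For a prognostic analysis it is a reason to go beyond them. If therapy affects the chance of sitting or walking, and use of therapy differs between the levels of a factor, a table of milestone proportions by that factor combines two things: the factor's association with outcome at a given therapy, and the difference in therapy between its levels. A single table cannot separate them. The same applies to factors that are related to one another, such as SMN2 copies and baseline motor status.

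At stake is what a clinician may take from the table. A factor could look important only because patients at one level were treated differently, or look unimportant because the patients with the worse outlook received the more effective therapy. Longer follow-up and complete data do not cure this.

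**Working it through.** **What can be reproduced.** The article gives no milestone rate, sample size or therapy distribution for this analysis, so there is no figure to reproduce and the size of the distortion in this registry cannot be calculated. What can be checked is whether the conditions for it are present, and how it behaves under assumed rates.

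**Conditions, from the document.**
- Therapy affects outcome: Introduction, where trial results are said to show an altered disease course.
- Therapy is not randomised: Treatment section.
- A named factor is related to outcome: SMN2 copies, Introduction.
- A named factor bears on a treatment decision: the Discussion sees few or no questions about treating pre-symptomatic patients with 2 or 3 copies, but "this question will undoubtedly arise for patients with 4 copies". This shows a link with the decision to treat before symptoms. It does not show its size, and it says nothing on the choice between therapies.

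**Formula.** Let *b* be the milestone rate without the therapy at the reference level of the factor, *f* the factor's difference at a given therapy, *d* the therapy's effect, and *p1*, *p0* the share receiving the therapy at the two levels. With additive effects:

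crude difference = (*b* + *f* + *d* × *p1*) − (*b* + *d* × *p0*) = *f* + *d* × (*p1* − *p0*).

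The difference within a therapy stratum is *f*. All rates below are assumptions, with *b* = 20%.

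**(a) Factor with no association of its own (*f* = 0).**

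| Use of therapy, *p1* vs *p0* | *d* = 20 points | *d* = 40 points |
|---|---|---|
| 50% vs 50% | 0 | 0 |
| 60% vs 40% | 32% − 28% = +4 (odds ratio 1.21) | 44% − 36% = +8 (1.40) |
| 70% vs 30% | 34% − 26% = +8 (1.47) | 48% − 32% = +16 (1.96) |
| 80% vs 20% | 36% − 24% = +12 (1.78) | 52% − 28% = +24 (2.79) |

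**(b) Factor with a true difference of +15 points, therapy used more at the unfavourable level.**

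| Use, favourable vs unfavourable | *d* = 20 points | *d* = 40 points |
|---|---|---|
| 50% vs 50% | 45% − 30% = +15 | 55% − 40% = +15 |
| 40% vs 60% | 43% − 32% = +11 | 51% − 44% = +7 |
| 30% vs 70% | 41% − 34% = +7 | 47% − 48% = −1 |
| 20% vs 80% | 39% − 36% = +3 | 43% − 52% = −9 |

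**(c) Two therapies.** Suppose sitting is 60% and 80% at the less and more favourable level under therapy A, and 30% and 50% under therapy B: a 20-point difference under each. If A goes to 80% of the less favourable and 20% of the more favourable group, the crude rates are 0.8 × 60 + 0.2 × 30 = 54% and 0.2 × 80 + 0.8 × 50 = 56%, a difference of 2 points. With the allocation reversed they are 0.2 × 60 + 0.8 × 30 = 36% and 0.8 × 80 + 0.2 × 50 = 74%, a difference of 38 points.

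**Reading.** With equal use of therapy the crude comparison is right. Otherwise it moves in either direction by *d* × (*p1* − *p0*), and can change sign. Comparison within therapy returns the assumed 0, 15 or 20 points in every case.

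**The case against.** The strongest reply is that this is one sentence in the Discussion of a journal article, that covariates and model form belong in the full protocol and SAP, and that the analysis is descriptive. Several parts of this stand.

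- A reader might infer that therapy is excluded. It is not: the list is open, and comparing frequencies does not rule out cross-classification by therapy.
- The analysis is already restricted by SMA type, and the Patients section defines type by age at onset, SMN2 copies and motor function. This removes part of the mixing between factors and severity.
- A reader might infer that prognostic factors are a registry objective. The objectives at the end of the Introduction do not list them. The Introduction raises them as a question for practice, and the Discussion expects possible insight.
- The proportion of sitters by copy number under current care is a legitimate descriptive quantity. It misleads only when read as the factor's association with therapy held fixed.
- The article partly acknowledges the problem. It says that comparisons may be limited by population differences and that findings will reflect heterogeneity of care.

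What does not stand is that the matter is simply left to the SAP. The article does not stay silent: it says that statistics will be limited to the simple comparisons. A regression in the SAP would depart from that text. The general caveats do not say how therapy will be handled here. The strata in the Data analysis section would not fill the gap as they are, because therapy at enrollment misses later additions and withdrawals.

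**Conclusion.** The concern holds for a secondary, descriptive analysis. The Discussion fixes a restriction that its own reason does not justify, and the therapy stratification elsewhere is not extended to the prognostic comparison. The crude proportions describe outcome under current prescribing and can understate, overstate or reverse a factor's association at a given therapy.

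This rests on two assumptions: that therapy affects the milestone, which the article supports, and that its use differs between factor levels within an SMA type, which free choice by physicians makes plausible but the article does not demonstrate. The figures (0 shown as +4 to +24; +15 as +11 to −9; 20 as 2 or 38) are illustrations, and their upper ends use large therapy effects and very uneven prescribing. With a 20-point effect and 60/40 use the shift is 4 points.

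A reader might go further and conclude that the registry's prognostic results will be wrong by tens of points, or that choice of therapy is known to differ between patients with 2 and 3 SMN2 copies. The document supports neither. Its remark on copy number concerns pre-symptomatic treatment and sets 4 copies apart from 2 or 3.

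**What to change.** In the Discussion, and wherever the full plan repeats it, remove for this analysis the limit to means, frequencies and trends. Then state:

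1. Milestone proportions by factor will be shown within therapy strata, including untreated. Strata are defined by therapy received before the milestone or censoring, not by therapy at enrollment alone.
2. Where numbers allow, a multivariable model will be added for each milestone, with SMN2 copies, age or time since diagnosis at a common origin such as enrollment, baseline motor status, and therapy. Where milestone dates exist, it should be a time-to-event model with time-updated therapy, because a fixed therapy covariate mishandles therapies added or withdrawn later. A common origin is needed because time from treatment start is undefined for untreated patients.
3. Adjusted estimates with 95% CIs will stand beside the crude proportions, which are labelled as descriptive of current care.

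Table 2 already lists SMN2 copies, date and age of diagnosis, motor assessments, the gene therapy date, and start and stop dates for other treatments. It does not list age at onset, which is why diagnosis is the practical reference. The cost is a change of wording and modest programming. The downside is that small SMA-type groups can carry few covariates; there, the stratified proportions alone should be shown.
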